### Study objectives

The primary objective of ADRISK is to show that addition of pembrolizumab to aRCT with cisplatin improves EFS compared with aRCT alone in locally advanced intermediate and high-risk HNSCC after surgery. The primary endpoint EFS is defined as time from randomization to the first event, i.e.:

locoregional or distant recurrence (relapse),occurrence of further malignant disease (independent from localization and type),death from any cause, andinitiation of a new anti-cancer treatment without a previous event (primarily in case of safety concerns/toxicities observed which must be addressed in the patient**’**s treatment).

Secondary goals of the trial are to show that addition of pembrolizumab to aRCT with cisplatin improves OS compared with aRCT alone in locally advanced intermediate and high-risk HNSCC and to assess toxicity and show that addition of pembrolizumab to aRCT with cisplatin is safe in terms of toxicity (early *and* late toxicity). The duration of patients**’** observation is planned for at least 24 months post randomization, but preferably until LPLV (last patient**’**s last visit after 24 months of observation) to collect endpoint-events as comprehensive as possible.

Within the trial PD-L1 and p16 (only at tumor site oropharynx) expression in tumor tissue will be characterized by immunohistochemistry to explore the relationship between tumor PD-L1 and p16 expression and response to treatment with pembrolizumab. Therefore, material collected during the tumor resection will be analyzed locally at trial site and validated by reference pathologists in the central lab.

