#### Pembrolizumab treatment

The experimental treatment to be used in this trial is outlined in **Table 3**. First cycle of pembrolizumab starts on day 1 of aRCT. Pembrolizumab should be administered at least 30 minutes prior to premedication for the chemotherapies. Furthermore, pembrolizumab should be administered prior to chemotherapy. Adverse events (both non-serious and serious) associated with pembrolizumab exposure may represent an immunologic etiology. These adverse events may occur shortly after the first dose or several months after the last dose of treatment. Pembrolizumab must be withheld for drug-related toxicities and severe or life-threatening AEs. Dosing interruptions are permitted in the case of medical/surgical events or logistical reasons not related to study therapy (e.g., elective surgery, unrelated medical events, patient vacation, and/or holidays). Subjects should be placed back on study therapy within 3 weeks of the scheduled interruption, unless otherwise discussed with the sponsor. The reason for interruption should be documented in the patient’s study record.

**Table 3 T3:** Pembrolizumab treatment.

Drug	Dose	Frequency Dose	Route of Administration	Regimen/Treatment Period
Pembrolizumab	200mg	q3w	intravenous infusion	Day 1 of each 3 week cycle over 51 weeks

Pembrolizumab should be administered on day 1 of every three-week cycle, repeat every 3 weeks (+/- 3 days; due to administrative reasons) until regular end of treatment (18 cycles, week 52), disease recurrence or premature termination for other reasons. All trial treatments can be administered on an outpatient basis, depending on the respective standard of the center. (Potential) outpatient basis means that trial treatments always take place in a clinic with medical personnel that is sufficiently trained for such emergency situations (e.g. severe infusion reactions). The appropriate emergency care is guaranteed and will be provided immediately. Pembrolizumab 200 mg will be administered as 30 minutes intravenous infusion every 3 weeks. Sites should make every effort to target infusion timing to be as close to 30 minutes as possible. However, given the variability of infusion pumps from site to site, a window of -5 minutes and +10 minutes is permitted (i.e., infusion time is 30 minutes: -5 min/+10 min).

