### Schedule of trial procedures

**Table 4** summarizes the trial procedures to be performed as planned or at unscheduled time points if deemed clinically necessary by the investigator.

**Table 4 T4:** Schedule of trial procedures.

Trial period	Baseline (BL)	V1 – V4 Safety Follow-up	C1 – C18 Pembrolizumab treatment		V5 – V12 (V13 - V16 optional) Efficacy/Safety Follow-up	SV1, SV2… Survival Follow-up
Time	ALL patients		only patients in EXPERIMENTAL arm		ALL patients	ALL patients AFTER disease RECURRENCE
day **–** 10 - day 0	weeks 1, 4, 7, 10 (+/- 3 days)	**day 1** (week 1) **of aRCT** Cycle 1	week 4 - 52 (every 3 weeks) (+/- 3 days) Cycles 2 - 18	month 3, 6, 9, 12 (+/- 7 days) month 15, 18, 21, 24 (+/- 14 days) every 6 months (+/- 28 days) thereafter - optional	every 6 months after recurrence
Administrative procedures						
Informed consent	X					
Eligibility criteria	X		X^1^			
Demographics/Medical history	X					
Registration Randomization	X^2^					
Prior/concomitant medication	X	X^3^	X	X	X	
Treatment						
Adjuvant radio-chemotherapy		X				
Pembrolizumab			X	X		
Anticancer therapy after recurrence						X
Clinical Procedures/Assessments						
Adverse Events		X^3^	X	X	X^4^	
Physical examination	X	X^3^	X	X	X	
Vital signs	X	X^3^	X	X	X	
ECOG status	X	X^3^	X	X	X	
Laboratory measurements	X	X^3^	X	X	X^5^	
Survival status; locoregional or distant recurrence, initiation of a new anti-cancer treatment		X^3^	X	X	X	X
Efficacy measurements						
Clinical endoscopic assessment	X				X	
CT or MRI Head and Neck	X				X^6^	
CT chest	X				X^7^	

V= visit; C= 3-week cycle (q3w) pembrolizumab infusion (and aRCT) starting on day 1 of each cycle; SV, survival visit.

^1^If results of laboratory procedures done at Baseline Visit are older than 10 days, new blood sampling are necessary prior to start of treatment with pembrolizumab. Furthermore, pregnancy test must be negative within 3 days prior to receiving the first dose of study medication.

^2^Randomization must be done by the day 1 (start of the trial treatment) at the latest.

^3^In control arm all clinical procedures/assessments should correspond with the experimental arm (three-weekly +/- 3 days) up to and including first efficacy follow-up (month 3 after randomization).

^4^In experimental arm: until 90 days following cessation of treatment, or up to initiation of a new anti-cancer treatment; in control arm: until 1^st^ efficacy-FU (month 3).

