### Plan for further treatment

Radiochemotherapy treatment in both groups takes maximal seven weeks. Pembrolizumab will be given in the experimental group over a period of 51 weeks. If patient responds to treatment no further therapy is necessary. If a patient experiences a disease recurrence (primary endpoint) detected by radiographic imaging, standard of care treatment outside the trial protocol is necessary, which is up to the discretion of the treating physician/investigator. Further observation for OS takes place.

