#### Planned methods for analysis

Confirmatory analysis follows the intention to treat principle and will be based on the full analysis set. Time to event endpoints will be analyzed by Cox regression with arm as fixed effects, stratification criteria as fixed and center as random effect. The occurrence of safety endpoints (AE by Preferred Term/occurrences of toxicities of grades ≥3) will be compared by chi-square tests. Odds ratios with 95% confidence intervals will be provided. Serious adverse events will be reported descriptively (including a clinical causality assessment) by System Organ Class and Preferred Term according to MedDRA. In case of relevant frequencies of SAE and classified serious adverse reactions (by Preferred Term) exact Fisher test will be applied on SAE/SAR occurrences. No confirmatory subgroup analyses are planned. PD-L1 status will be analyzed in exploratory analyses. Safety issues will be carefully monitored. Regular safety analyses will be performed and presented to the Data-Monitoring Committee (DMC). Statistical monitoring will focus on data quality assurance. All analyses will be pre-specified in a detailed statistical analysis plan, which will be finalized before data base closure. The trial will be reported according to CONSORT criteria.

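### Control-arm AE recording stops at month 3 while experimental-arm recording continues to 90 days after treatment, so late toxicity cannot be compared between arms on scheduled AE records

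*Protocol article*

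**What the plan says.** All places are in the protocol article.

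- **Schedule of trial procedures, Table 4, footnote 4** sets the AE recording period by arm. Experimental: "In experimental arm: until 90 days following cessation of treatment, or up to initiation of a new anti-cancer treatment". Control: "in control arm: until 1^st^ efficacy-FU (month 3").
- **Table 4, footnote 3** aligns the arms, but only up to and including the month 3 visit: "In control arm all clinical procedures/assessments should correspond with the experimental arm (three-weekly +/- 3 days").
- **Study objectives** includes the secondary goal of showing that adding pembrolizumab "is safe in terms of toxicity (early *and* late toxicity"). The 24 months of observation are justified separately, "to collect endpoint-events as comprehensive as possible".
- **Planned methods for analysis**: "The occurrence of safety endpoints (AE by Preferred Term/occurrences of toxicities of grades ≥3) will be compared by chi-square tests", with odds ratios and 95% confidence intervals. No time window is given. Details are deferred to an SAP.
- **Pembrolizumab treatment** says of AEs associated with pembrolizumab exposure: "These adverse events may occur shortly after the first dose or several months after the last dose of treatment". It places cycle 18 in week 52.
- **Plan for further treatment**: "Radiochemotherapy treatment in both groups takes maximal seven weeks".

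**The concern.** Both arms receive the same radiochemotherapy and so carry its late effects, but after month 3 those effects are scheduled to be recorded as AEs in one arm only. Control recording closes about six weeks after radiochemotherapy ends. An event in month 8 enters the AE data if the patient was randomised to pembrolizumab and is still within the recording window. In control it does not.

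Two things are at stake. First, a between-arm statement on late toxicity has no control AE records behind it. Second, a chi-square test on occurrence counts patients and ignores how long each was observed. If it is run on everything recorded, later events can count only against pembrolizumab, and a true excess cannot be told apart from longer recording.

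**Working it through.** **1. Recording windows (calendar arithmetic).** Cycle k starts on day 1 + 21(k − 1).

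- Cycle 18: 1 + 21 × 17 = day 358, the first day of week 52. This reproduces the week stated under Pembrolizumab treatment.
- Completer: 358 + 90 = day 448. Counting from the end of the last cycle (20 days later) gives day 468.
- Stop after cycle 9: 169 + 90 = day 259. After cycle 3: 43 + 90 = day 133. After cycle 1: 1 + 90 = day 91, the same as control. If cessation also covers radiochemotherapy, a patient stopping at cycle 3 is recorded to 49 + 90 = day 139.
- Control: month 3 = 3 × 365.25/12 ≈ day 91.
- Ratio for a completer: 448/91 = 4.9. After radiochemotherapy (day 49): 448 − 49 = 399 days against 91 − 49 = 42 days.
- Scheduled AE contacts: five in control (weeks 1, 4, 7, 10 and month 3); in the experimental arm up to 18 cycles plus the month 3, 6, 9 and 12 visits.

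**2. What continues in control after month 3.** Table 4 keeps physical examination, vital signs, ECOG, concomitant medication, endoscopy, survival status and new anti-cancer treatment at the visits to month 24, with head and neck imaging every 6 months and chest CT every 12. By footnote 4, only AE recording stops.

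**3. Size of the bias if all recorded AEs are compared.** The document gives no AE rates, so these are assumptions: 120 per arm (240 randomised 1:1); identical true risk in both arms; incidence p0 by day 91; a further rate r per year afterwards. Then

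- control: p_C = p0
- experimental, recorded to day D: p_E = 1 − (1 − p0) × exp(−h(D − 91)), with h = −ln(1 − r)/365.25

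Example, p0 = 0.10, r = 0.05, D = 448: h = 0.05129/365.25 = 0.0001404; h × 357 = 0.0501; p_E = 1 − 0.90 × 0.9511 = 0.144; OR = (0.144/0.856)/(0.10/0.90) = 1.51.

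The mixed scenario takes 50% to day 448, 25% to day 259 and 25% to day 133 (mean 224 + 64.75 + 33.25 = 322 days). Rejection is the exact probability that a two-sided 5% Pearson chi-square test is significant.

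| p0 | r per year | OR, all complete | Rejection | OR, mix | Rejection |
|---|---|---|---|---|---|
| 0.10 | 2% | 1.20 | 7% | 1.13 | 6% |
| 0.10 | 5% | 1.51 | 18% | 1.33 | 11% |
| 0.10 | 10% | 2.08 | 50% | 1.68 | 26% |
| 0.50 | 2% | 1.04 | 5% | 1.03 | 5% |
| 0.50 | 10% | 1.22 | 11% | 1.14 | 7% |

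With equal windows and p0 = 0.10, rejection is 5.2%.

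**4. Plausibility of the columns.** The design's 70% two-year EFS implies, under an exponential curve, 1 − 0.70^(358/730.5) = 16% with an EFS event by day 358. Not every patient can complete, so the mixed columns are the more realistic ones and the 50% figure is an upper illustration.

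**The case against.** The strongest reply is that the article names no analysis window. A reader might infer that the chi-square tests do set unequal windows against each other. The document does not say so: it defers detail to an SAP, and footnote 3 makes a like-for-like comparison to month 3 available without changing the protocol. This stands, and the odds-ratio bias is conditional on all recorded AEs being used.

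A reader might also infer that control has no safety data after month 3. That goes too far. Examination, vital signs, ECOG, concomitant medication, endoscopy and imaging continue and could show some late local effects of radiotherapy. The analysis section treats SAEs separately, and the full protocol may collect them for longer. What is missing is scheduled AE recording.

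Third, the late-toxicity goal need not be comparative. The article does not define late toxicity, and the 24 months are tied to endpoint events. A completer is recorded for about 13 months after radiochemotherapy (399 days), which can support a descriptive statement. Longer recording under a longer treatment is also sensible for describing that arm.

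Finally, the late rates are assumed, and the bias runs against pembrolizumab, so it would not produce a false claim of safety.

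None of this removes the core point. Footnote 4 is an explicit collection rule. An SAP can restrict the test to month 3, but it cannot recover control AEs that were never recorded.

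**Conclusion.** The concern holds in a limited form. After month 3 no AE recording is scheduled in control, while it continues to about day 448 in an experimental-arm completer and for less time in early stoppers. Late toxicity therefore cannot be compared between arms on scheduled AE records. This rests on footnote 4 and calendar arithmetic, not on any assumed rate.

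The bias in the odds ratios is conditional on comparing all recorded AEs, and its size rests on the assumed late rates and stopping pattern. It is small for common early toxicities (about 1.03 to 1.22) and moderate for uncommon later-onset terms (about 1.1 to 1.7 with a mix of early stoppers). The EFS analysis is not affected.

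**What to change.** **Wording, at no data cost.** State that between-arm comparisons of AEs by Preferred Term and of grade ≥3 toxicities use only the shared window to month 3. Report later experimental-arm AEs descriptively. Word the late-toxicity goal as descriptive for the experimental arm.

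**Where still feasible, added collection.** After the current AE windows close, record grade ≥3 and immune-related events in both arms at the existing visits to month 24, flag onset after a new anti-cancer treatment, and compare these events over a common window. In control this means up to seven existing visits (months 6, 9, 12, 15, 18, 21 and 24).

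The added collection needs a case report form change, with data entry, coding and monitoring. Recruitment began in August 2018, so data will be incomplete for patients already past those visits or in survival follow-up. Experimental patients on treatment are seen every three weeks against every three months in control, so detection still differs to about month 12. Lower-grade late effects and laboratory-only events may still be missed.

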### Plan for further treatment

Radiochemotherapy treatment in both groups takes maximal seven weeks. Pembrolizumab will be given in the experimental group over a period of 51 weeks. If patient responds to treatment no further therapy is necessary. If a patient experiences a disease recurrence (primary endpoint) detected by radiographic imaging, standard of care treatment outside the trial protocol is necessary, which is up to the discretion of the treating physician/investigator. Further observation for OS takes place.

### Statistical methods

#### Estimation of sample size

We expected a 2yr EFS of 55% with aRCT alone based on Cooper et al. (3, 15) and Bernier et al. (2) and assumed proportional hazards. A hazard ratio of 0.6 corresponds to an increase in EFS rates (at ~2 years) from e.g. 55 to 70% - an effect size worth detecting. Requiring a 5% one-sided significance level and 80% power, we need to observe at least 93 events for inference with the log rank test or by Cox regression. Since the effect of the experimental treatment is expected to become apparent only after 3-4 months, and the power may be slightly reduced, we set a target of 100 events. The number of patients needed to observe this count depends on the times of accrual, follow-up as well as the strategy of FUP. After modeling the expected information flow and calculating the expected observed events since start of accrual (using the pooled EFS curve in Cooper et al. (3)), we specified the end of study after 2 years of last patient’s observation or when at least 100 events have been observed before that time.

#### Analysis population

The full analysis set (FAS, also called intention-to-treat (ITT) population) includes all randomized patients who start with the trial-related interventions. Randomized patients who withdraw their informed consent before the 1st trial intervention takes place will be excluded from the FAS.

The per-protocol (PPS) set is defined by all patients belonging to the ITT without major violations of the study protocol. Beside violations of eligibility criteria and patients not treated as randomized further protocol violations occurring during study conduct are reviewed and classified as major in the statistical analysis plan independently from arm allocation.

The safety population is defined by all randomized patients belonging to the FAS. In safety analyses, patients will be classified whether or not they received at least a single Pembrolizumab dose, irrespective of the randomized group allocation.

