## Methods

### Study design

ADRISK is a prospective, randomized, open-label, two-armed phase II multicenter superiority trial within the German Interdisciplinary Study Group of German Cancer Society (IAG-KHT). Patients with primary resectable stage III and IV (according to 7^th^ edition of TNM classification) HNSCC of the oral cavity, oropharynx, hypopharynx and larynx with pathologic high (R1, extracapsular nodal extension) or intermediate risk (R0 <5 mm; N≥2) after surgery who are eligible for cisplatin-based aRCT after surgery will receive either standard aRCT with cisplatin versus the same treatment + pembrolizumab (200 mg iv, in 3-week cycle, max. 12 months) (**Figure 1**). This clinical trial has been approved by the ethics committee of the University of Leipzig (076/18-ff).

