### Randomization process

Randomization of patients between experimental and control arm is performed centrally *via* a secure web-based tool using a modified minimization procedure with stochastic component according to Pocock (14) in a 1:1 proportion. Stratification is performed using the tumor localizations: 1) oral cavity, 2) oropharynx, 3) larynx, or 4) hypopharynx. For patient with oropharyngeal carcinoma, the p16-marker is generally determined in routine procedures and will be used as sub-classifier 2+) and 2-) so that 5 strata will be used in total. Furthermore, a stratification according to the q3w vs. q1w schedule of chemotherapy will be applied. Randomization will be balanced according to trial site as well. The result of the successful randomization is immediately available *via* the randomization tool and is forwarded automatically to the investigator and the Clinical Trial Center Leipzig.

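### The analysis set labelled ITT is a modified ITT set: it leaves out randomized patients who never start treatment, in an open-label trial where the arm is already known

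*Protocol article*

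**What the plan says.** In the protocol article, Analysis population names one set for efficacy: "The full analysis set (FAS, also called intention-to-treat (ITT) population"). It states that this set "includes all randomized patients who start with the trial-related interventions", and adds: "Randomized patients who withdraw their informed consent before the 1st trial intervention takes place will be excluded from the FAS". The safety population is then defined as the randomized patients in that same FAS, so the efficacy and safety sets contain the same people. The article describes no set of all randomized patients.

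Planned methods for analysis makes this the primary set: "Confirmatory analysis follows the intention to treat principle and will be based on the full analysis set".

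Four other statements bear on the point:

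- Study design: "ADRISK is a prospective, randomized, open-label, two-armed phase II multicenter superiority trial".
- Randomization process: "The result of the successful randomization is immediately available", and it is forwarded automatically to the investigator.
- Schedule of trial procedures, Table 4, footnote 2: "Randomization must be done by the day 1 (start of the trial treatment) at the latest". Table 4 itself places randomization in the baseline column, which covers day -10 to day 0.
- Study objectives: "The primary endpoint EFS is defined as time from randomization to the first event".

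**The concern.** An intention-to-treat set is fixed at randomization. This one is fixed later, when treatment starts, so the definition and the stated principle disagree. The definition is explicit in the article and is not a detail deferred to the analysis plan.

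Leaving out non-starters does little harm when knowledge of the arm cannot influence whether a patient starts. Here it can: patient and investigator know the allocation before the first intervention. A patient disappointed by allocation to control, for example, may decline to begin. Any such loss would be selective, and the confirmatory EFS comparison would no longer rest fully on randomization.

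The set also fits poorly with the endpoint. The EFS clock starts at randomization, so a relapse, death or new anti-cancer treatment before the first intervention is an EFS event. If that patient then never starts, both patient and event leave the primary analysis.

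**Working it through.** **1. The plan's own figure.** Estimation of sample size gives 2-year EFS of 55% versus 70%, one-sided 5% significance, 80% power and at least 93 events, with a target of 100.

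- HR = ln(0.70)/ln(0.55) = 0.5966.
- Schoenfeld, 1:1: events = 4 × (1.645 + 0.842)² / (ln 0.5966)² = 92.7, rounded up to 93. This reproduces the stated figure. With the rounded HR of 0.60 the result is 94.8, i.e. 95.
- Power at 100 events and HR 0.60 is 81.8%.

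Nothing in this calculation depends on how the FAS is defined.

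**2. Loss of power if both arms lose patients equally.** Assume events fall in proportion to patients.

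| Excluded of 240 | Events | Power (HR 0.60) |
|---|---|---|
| 2% (5) | 98 | 81.2% |
| 5% (12) | 95 | 80.1% |
| 10% (24) | 90 | 78.2% |

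Power is barely affected. The issue is bias.

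**3. Shift in one arm's 2-year EFS.** Let f be the share of the arm excluded, R the EFS of those retained and Q the EFS of those excluded. The whole arm has EFS (1 − f)R + fQ, so the retained patients differ from the whole arm by f(R − Q) = f × d, where d is the difference between excluded and retained.

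- f = 0.05, d = 0.20: 0.05 × 0.20 = 0.010, or 1.0 point.
- Low end, f = 0.03, d = 0.10: 0.3 point.
- High end, f = 0.08, d = 0.30: 2.4 points.

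The planned difference is 70 − 55 = 15 points. The documents give neither f nor d; both are assumptions.

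**4. What this could do to the type I error.** Assume no true effect, 2-year EFS of 55% in both arms as randomized, 100 events, and loss in one arm only. The EFS of the retained patients is (0.55 − fQ)/(1 − f). The apparent HR is the ratio of the log EFS values (experimental over control). The one-sided error is Φ(−ln HR × √(100/4) − 1.645).

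For f = 5% (6 of 120):

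| Arm losing patients | EFS of those lost | Apparent HR | Type I error |
|---|---|---|---|
| Control | 70% | 0.976 | 6.4% |
| Experimental | 40% | 0.976 | 6.4% |
| Experimental | 25% | 0.953 | 8.0% |
| Control | 40% | 1.024 | 3.9% |
| Control | 25% | 1.050 | 3.0% |

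With 10% lost (12 of 120), the first three rows become about 8%, 8% and 13%, and the last two 2.9% and 1.5%. The direction depends on who is lost and from which arm.

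**The case against.** The case for leaving the definition alone has real substance.

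- **Same first intervention, short interval.** Radiochemotherapy starts on day 1 in both arms, with the first pembrolizumab cycle on the same day. Randomization falls within about ten days before that and may be as late as day 1. A patient who deteriorates in the interval faces the same radiochemotherapy in either arm, so that loss is not arm-dependent in itself. This stands, and few exclusions should be expected.
- **Early events.** A reader might infer that every event between randomization and day 1 is lost. The text does not support that. It excludes non-starters, not events, so an early event disappears only if the patient never begins treatment. Entry requires macroscopically complete resection and ECOG 0 or 1, so such cases should be isolated.
- **Consent withdrawal as a second exclusion.** Patients who withdraw before the first intervention are normally non-starters already. That sentence can be read as explaining the rule rather than adding to it.
- **Limited repair.** A patient who withdraws and is censored within days of randomization enters almost no risk set and adds almost nothing to the Cox estimate. The gain comes mainly from non-starters who stay in follow-up. The shift in step 3 supposes 2-year outcomes for all excluded patients, so it overstates what the change would recover.

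None of this removes the contradiction between the definition and the stated principle, or the possibility of selective loss once the arm is known.

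**Conclusion.** The point holds at moderate severity. The confirmatory set is a modified ITT set under an ITT label, and it allows exclusion after randomization with the arm known.

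If 5% of one arm were excluded with a 2-year event risk 20 points away from those retained, that arm's EFS would move by 1.0 point (0.3 to 2.4 for 3–8% excluded and a 10–30 point difference), in either direction. A type I error clearly away from 5% needs both one-sided loss and a marked prognostic gap. All of these rates are assumed, because the documents give no non-start rate.

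A reader might go further and conclude that arm-dependent exclusion will occur, or that the EFS result could not be relied on. The documents do not support either. They show only that the rule permits such exclusion, and the shared day-1 start makes it likely to be rare.

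**What to change.** - Define the primary set for EFS and OS as all randomized patients, analysed as allocated, whether or not treatment starts.
- Continue follow-up of non-starters who have not withdrawn consent.
- Censor patients who withdraw consent at last contact, using survival status where consent allows, and acknowledge that this recovers little information for them.
- Keep the current set under the name modified ITT, as a sensitivity analysis and for safety.
- Report non-starters by arm, with reasons.

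The cost is one changed definition and some follow-up of non-starters. The 93-event requirement and the 100-event target stay as they are. The article says the analysis plan will be finalized before the database is closed, so the definition can be corrected before the final analysis.
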